#### Secondary Pilot Clinical Trial Effectiveness Outcomes

As a proxy outcome measure for clinical effectiveness, each clinical visit for the control and intervention groups will be assessed using the review of visit checklist shown in Figure 5 by the therapists leading the clinical visit. Then, 2 independent raters, who are seating specialists, will assess the checklist for each participant and will be blinded to the identities of the patients and therapist. The reviewers will rate the visit information on a 5-point Likert scale (eg, “Rate the effect of AW-Shift data on clinical recommendations: (1) significantly diminished, (2) diminished, (3) neither improved nor diminished, (4) improved, or (5) significantly improved”). The reviewer ratings will be analyzed with a 2-sample Mann-Whitney *U* test to determine if the ratings are different between groups to test our hypothesis that the AW-Shift data will significantly improve clinical recommendations. Effectiveness will also be assessed qualitatively in the interviews.

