#### Control Protocol

If participants are randomized into the control group, the standard of care protocol will be followed as used in the seating clinic. Demographic and additional variables will be collected from participants similar to those in the intervention group, and their clinical visit will be recorded for assessment of the visit.

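### The secondary effectiveness test compares the arms on a rating of AW-Shift data, which control visits do not have, so it does not compare the quality of recommendations

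*Protocol article*

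**What the plan says.** Under Secondary Pilot Clinical Trial Effectiveness Outcomes, the protocol article states that "each clinical visit for the control and intervention groups will be assessed using the review of visit checklist". The therapist leading the visit completes that checklist. Two independent seating specialists then work from it; they "will assess the checklist for each participant and will be blinded to the identities of the patients and therapist". They rate the visit information on a 5-point scale, and the one item printed, introduced as an example, is "Rate the effect of AW-Shift data on clinical recommendations". Its scale runs from significantly diminished (1) to significantly improved (5), with the midpoint labelled "3) neither improved nor diminished".

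On the analysis, the section says: "The reviewer ratings will be analyzed with a 2-sample Mann-Whitney" U test between groups, "to test our hypothesis that the AW-Shift data will significantly improve clinical recommendations".

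The Study Design section for aim 3 assigns the connected care model with AW-Shift to 26 participants and standard of care to the other 26. Study Procedures describes the two weeks of AW-Shift use at home as the start of the intervention. For controls, the Control Protocol section says that "the standard of care protocol will be followed as used in the seating clinic"; it mentions no home use of the system.

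**The concern.** A two-sample test is informative only if the measured quantity has the same meaning in both samples. Here the printed item asks about the effect of a data source that exists in one arm only. A rater with a control checklist can mark the midpoint, because absent data neither helped nor harmed, or leave the item blank. No instruction says which.

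Neither choice yields a between-arm comparison of recommendations. A difference in ratings would show that raters judged the AW-Shift data helpful in some intervention visits. It would not show that those patients received better recommendations than controls did. The article calls this outcome a proxy for clinical effectiveness, attaches a formal hypothesis to it, and intends the pilot to inform a full trial, so a p-value from this test could be read as evidence of benefit that it does not carry.

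Masking adds to the problem. The stated blinding covers patient and therapist identity. Masking to arm is not stated, and the item names the intervention.

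**Working it through.** The article states no power, effect size or expected rating distribution for this outcome, so there is no figure to reproduce. The check is what the test would measure and how few ratings could move it.

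**Inputs from the document**
- 26 participants per arm (Study Design; Sample Size).
- Two-sided tests at 0.05 (General Statistical Methods).
- Scale 1 to 5 with neutral midpoint 3, Mann-Whitney U test (Secondary Pilot Clinical Trial Effectiveness Outcomes).

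**Assumptions, not in the document**
- One rating per participant.
- All 26 controls score 3.
- The intervention distributions shown below.

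**Step 1: controls marked not applicable.** There is no second sample and the test cannot be run.

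**Step 2: controls all at 3.** Let k intervention visits score 4, m score 2 and the rest 3.
- U = 26×26/2 + 13(k − m) = 338 + 13(k − m).
- Tie-corrected variance = (26×26/12) × [53 − Σ(t³ − t)/(52×51)], where t is the number of ratings at each score.
- z = (|U − 338| − 0.5)/SD, with continuity correction.

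For k=4, m=0:
- U = 390.
- The tie sum is (48³ − 48) + (4³ − 4) = 110,604.
- SD = 25.22, z = 51.5/25.22 = 2.04, p = 0.041.

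For k=4, m=1:
- U = 377.
- The tie sum is (47³ − 47) + (4³ − 4) + 0 = 103,836.
- SD = 27.93, z = 38.5/27.93 = 1.38, p = 0.168.

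| Intervention ratings (of 26) | Mann-Whitney p |
|---|---|
| three 4s, rest 3 | 0.081 |
| four 4s, rest 3 | 0.041 |
| five 4s, rest 3 | 0.021 |
| four 4s, one 2, rest 3 | 0.168 |
| six 4s, two 2s, rest 3 | 0.133 |

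**Step 3: exact cross-check.** With no score below 3, Fisher's two-sided p = 2·C(26,k)/C(52,k). This gives 0.110 at k=4, 0.051 at k=5 and 0.023 at k=6, so the exact test needs six visits.

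**Step 4: how often the test would reject.** If no rating is below 3 and a share q of intervention visits is rated 4, rejection requires at least 4 of 26. By the binomial tail, the probability is 0.26 at q=0.1, 0.79 at q=0.2 and 0.97 at q=0.3.

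Simulations (4,000 replicates, controls fixed at 3) gave the following rejection rates for assumed intervention shares at scores 1 to 5:

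| Shares at 1/2/3/4/5 (%) | Controls all at 3 | Same distribution in both arms |
|---|---|---|
| 0/10/40/40/10 | 88% | 4% |
| 0/5/55/35/5 | 88% | 4% |
| 0/0/70/30/0 | 97% | 5% |
| 5/20/50/20/5 | 8% | 5% |

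If every intervention rating is 3, rejection is 0. The last column represents an item that can be answered in both arms when recommendations do not differ: the test then holds about its nominal level. With the printed item, rejection is governed by how far intervention ratings lean from the midpoint, whatever the quality of the control recommendations.

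**The case against.** The strongest reply is that the item is only an example and that the checklist (Figure 5) is not shown. The raters' full form may contain items that apply to both arms, and a journal article need not print it. This stands as a limit on confidence. It does not remove the point, because the hypothesis attached to the test is itself about AW-Shift data, and the printed item is the authors' own illustration of what is to be compared.

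Controls might also be thought to have AW-Shift data: the Control Protocol section collects variables similar to those in the intervention group, and Additional Study Variables lists a home-use metric without naming an arm. Neither place says that controls receive the system, and Study Procedures defines its use as the intervention.

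Three stronger readings are tempting and are not supported:
- **That significance is settled in advance or nearly guaranteed.** Only the control side would be fixed. The scale runs both ways, and a few ratings below 3 are enough to remove significance.
- **That the raters know the arm.** The article says "will be blinded to the identities of the patients and therapist" and is silent on arm. The item makes unmasking likely, but what the checklist reveals cannot be seen.
- **That the two raters' scores would be stacked as independent observations.** The article does not say how they are combined, which is ordinary analysis-plan detail.

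It is also normal in a pragmatic trial for the treating therapist to record the visit; that is not a fault in itself.

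**Conclusion.** The point holds in limited form. As written, the between-arm test uses an item with no meaning for control visits. It contrasts intervention ratings with a neutral default, or has no comparator, and does not test whether recommendations are better with AW-Shift.

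The numerical illustration (four of 26 visits, p=0.041; six of 26 by the exact test) depends on all controls scoring 3 and no intervention visit scoring below 3. It shows how little could produce a significant result, not that one will occur.

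This should be fixed rather than must be fixed: the outcome is a secondary proxy in a 52-person pilot, and the primary clinical outcomes, implementation surveys and feasibility rates do not depend on it.

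**What to change.** For the between-arm test, replace the item with one that can be answered for any visit, for example how well the recommendations address the patient's documented seating and skin risks, scored 1 to 5. Reword the hypothesis to match: recommendations are rated higher in the intervention arm than under standard of care. State that the same two raters are masked to arm, and give them checklists with AW-Shift wording removed as far as possible. Keep the AW-Shift item as a descriptive measure in the intervention arm only.

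The cost is one reworded rating form and the work of redacting checklists, with the same visits and raters. The downside is that redaction may remove some detail relevant to judging the recommendations, and masking may remain incomplete. The change needs to be made before aim 3 ratings begin, because ratings gathered on an item that cannot be answered for controls cannot be repaired in the analysis.

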**Figure 5 figure5:**
[figure not shown]
Clinical visit review checklist.

#### Implementation Outcome Measures

Implementation success will be assessed using feasibility, acceptability, and appropriateness surveys regarding the in-home system use of participants and therapists. This information will guide the broad implementation of the intervention.

#### Additional Study Variables, Controls, and End Points

Demographic variables relevant to SCI/D will be collected and used in the analysis as appropriate. Additional metrics include self-efficacy in managing pressure, assessed using the Skin Care Belief Scales [40]; consistency of weight shift performance, as measured by the AW-Shift system during home use; and the SCI–Quality of Life scale.

#### Feasibility Study Variables

For future clinical trial planning, the study variables of screening rate, recruitment rate, enrollment rate, and retention rate will be measured. In addition, the treatment adherence rate and treatment fidelity rates will be measured, and the assessment process will be evaluated. The assessment process includes documenting the planned assessments and data collection instruments that are completed in addition to the duration of the visits.

#### Sample Size

The sample size for this pilot study (N=52; n=26, 50% per group) is based on guidance that for a trial with 90% power and 2-sided 5% significance, pilot trial sample size of 25 participants per treatment arm is sufficient for an expected small, standardized effect size (0.2) [39]. We do not have the needed data for our primary outcomes to directly determine the power of our planned study design; however, this pilot study will be used to power the full clinical trial. Furthermore, we have used approaches to optimize our statistical power including blocking within the design itself that adjusts for covariates during randomization to reduce imbalance and triangulating the findings of quantitative analyses with qualitative data in mixed methods designs [41].

#### Potential Limitations and Alternative Strategies

In addition to the potential limitation described for aim 2, aim 3 has the added potential of loss to follow-up. As the long-term follow-up data are passively extracted from the medical record, we acknowledged that patients may seek care outside the original health system they were recruited from. In addition, for participants who have data that we cannot access, we will seek the approval of the participant to access their medical records from other medical systems.

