#### Study Design

This single-site randomized controlled trial will use a modified intention-to-treat analysis. Randomization will be a stratified, block randomization with stratification based on wheelchair type (manual vs power) and current wound severity (no wound or stage 1 vs stage 2 or stage 3). The intervention group (26/52, 50%) will receive the connected care model that used AW-Shift in combination with telehealth. The control group (26/52, 50%) will receive the standard of care that uses telehealth when appropriate. The statistician will be masked to the group allocation information for the outcome measure analysis.

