#### Intervention Protocol

The planned intervention protocol is similar to that described for aim 2, for the rapid quality assessment as described in the *Protocol for Connected Care Model* section. We expect that the protocol will be improved through the iterative process we are using to optimize the implementation of our intervention. Full demographic variables relevant to SCI/D will be collected during the consent visit. The same surveys and structured interview will be completed after each visit by the intervention group participants and the therapists including assessment of usability (System Usability Survey [34]), acceptability (Unified Theory of Acceptance of Use of Technology [35,36]), feasibility (Feasibility of Intervention Measure [37]), and appropriateness [37] of the procedures.

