#### Primary Pilot Clinical Trial Effectiveness Outcomes

The primary effectiveness of the intervention will be captured via the collection of the following clinical outcomes: wound recurrence, early identification of wounds, wound healing, and hospital admission or readmission. The data for these metrics will be abstracted during the full year (365 days) after the study-related clinical visit for both the control and intervention group participants. Then, 2 independent therapist team members will abstract the medical records of each participant to search for the occurrence of an incident wound, stage at which wounds are identified, time frame of wound healing, and occurrence of a hospital admission or readmission directly related to a seating area pressure wound. Comparisons between groups for the primary outcome measures will be made using a 2-tailed *t* test. Additional comparisons will be made with regression and mixed effect models to explore the role of covariates on the study findings.

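### Access to outside records depends on the team already knowing of outside care, so wounds and admissions that leave no trace in the home chart may be missed and read as no event

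*Protocol article*

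**What the plan says.** The trial has one site: "This single-site randomized controlled trial will use a modified intention-to-treat analysis" (Protocol article, Aim 3, Study Design).

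Under Primary Pilot Clinical Trial Effectiveness Outcomes, the four primary measures are recurrence, early identification, healing and pressure-related admission. They are taken from charts: "The data for these metrics will be abstracted during the full year (365 days) after the study-related clinical visit". Two therapists on the team "will abstract the medical records of each participant to search for the occurrence of an incident wound" and the related details.

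Under Potential Limitations and Alternative Strategies for Aim 3, the authors state that "the long-term follow-up data are passively extracted from the medical record" and that "patients may seek care outside the original health system they were recruited from". The remedy they give is: "for participants who have data that we cannot access, we will seek the approval of the participant to access their medical records". No time point is attached to it.

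The Intervention Protocol mentions a consent visit but does not say whether a release for outside records is part of it. Under Ethical Considerations, ethics approval for aim 3 is still to be sought. Under Sample Size, the pilot is meant to supply the basis for powering the full trial.

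**The concern.** The remedy applies to participants whose data are known to be out of reach. With passive follow-up, the article describes nothing that would bring unknown outside care to the team's attention. A home chart with no wound entry looks the same for a participant who stayed wound-free and for one who was admitted elsewhere.

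Outside care is plausible on the article's own account. Eligibility asks only for a past or scheduled seating clinic visit, not for wound or inpatient care in the same system. The Discussion notes that patients often travel far for pressure mapping. The Background gives pressure injury as a cause of rehospitalization at 11% to 20% and links it to mortality. Loss among those who have died or become too ill to reach may therefore be related to the outcome.

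At stake are the event rates themselves, and with them the figures carried into the design of the full trial.

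**Working it through.** **What the stated rule does with each kind of participant**

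| Participant | Home chart | Does the remedy apply? | Likely reading |
|---|---|---|---|
| No wound | Silent | Not needed | No event (correct) |
| Wound treated at home site | Entry | Not needed | Event (correct) |
| Wound treated elsewhere, known to the team, participant agrees | Silent or partial | Yes | Event recovered |
| Wound treated elsewhere, known, participant dead or unreachable and no earlier approval | Silent or partial | Approval cannot be obtained | Unknown or missed |
| Wound treated elsewhere, no trace | Silent | Not triggered | May be read as no event |

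The last row is the gap. General Statistical Methods relies on mixed models, with multiple imputation as an option. Neither helps here, because an outcome read as no event is never flagged as missing.

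**Figures in the plan.** The article gives no loss to follow-up, no share of outside care and no expected event rate for this trial. The stated size is consistent: 26 × 2 = 52. The guidance it cites asks for 25 per arm. The one extra participant would cover at most 1/26 = 3.8% loss, and the article does not call it a dropout allowance.

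**Illustration.** Let p be the true risk and u the share of events treated elsewhere, never retrieved and read as no event. Then observed risk = p × (1 − u), and participants with a missed event per arm = 26 × p × u. All values of u are assumptions.

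With p = 40% (assumed) and u = 15%: 0.40 × 0.85 = 34%, and 26 × 0.40 × 0.15 = 1.6 participants per arm.

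The Background gives incidence of 25% to 38% and recurrence of up to 80%. These are not stated as one-year risks for this trial, so they serve only as a range:

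| p | u = 10% | u = 20% | u = 30% | Missed per arm of 26, u = 10% to 30% |
|---|---|---|---|---|
| 25% | 22.5% | 20.0% | 17.5% | 0.7 to 1.9 |
| 38% | 34.2% | 30.4% | 26.6% | 1.0 to 3.0 |
| 80% | 72.0% | 64.0% | 56.0% | 2.1 to 6.2 |

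**Equal loss and a real effect.** Take assumed true risks of 50% and 30%. The difference becomes 20 × (1 − u) points: 20, 18, 16 and 14 points at u = 0, 10%, 20% and 30%. Power with n = 26 per arm is Φ{[Δ − 1.96√(2p̄(1 − p̄)/n)] / √([p₁(1 − p₁) + p₂(1 − p₂)]/n)}, which gives 31%, 27%, 23% and 20%. At u = 20%, for example, the trial would see 40% against 24%.

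**Unequal loss, no real effect.** If one arm misses 10% and the other 30%, the false difference is p × 0.20: 5, 7.6 or 16 points at p = 25%, 38% or 80%. The sign depends on which arm loses more. Nothing in the article fixes either share.

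**The case against.** The strongest reply is that this is a condensed article. The content and timing of a record release belong to the consent form and full protocol, which are not shown, and aim-3 approval was still pending. The authors have also named the limitation and a remedy. The rule separating no event from no record is commonly left to an analysis plan or abstraction manual.

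Much of that stands, and it rules out several stronger readings:

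- A reader might infer that permission is sought only after data are found to be inaccessible. The text gives no time point and does not exclude approval at consent.
- A reader might infer that outside events are simply lost. The stated remedy would recover them for known outside users who agree.
- A reader might infer that silent charts will be scored as wound-free. No scoring rule is stated, so this is a risk and not a stated plan.
- A reader might infer that outside care will be discovered more often in the intervention arm, because "The same surveys and structured interview will be completed after each visit by the intervention group participants and the therapists" and because that arm has device support. The outcome data are "abstracted during the full year (365 days) after the study-related clinical visit for both the control and intervention group participants". The home use of about two weeks comes before that visit, and the one clinical visit described, with its surveys and interview, falls at about the start of the window. The article does not establish repeated contact over the following year.

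The reply does not remove the core. The article does not leave outside records to another document. It states a strategy, and that strategy is conditional on known inaccessible data while capture is passive.

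**Conclusion.** The point holds as a modest design weakness with a cheap remedy. Followed as written, the strategy would not reach outside wounds or admissions that leave no trace in the home chart, and the planned missing-data methods would not repair this. Event rates may be undercounted. The size cannot be taken from the article: with assumed losses of 10% to 30%, the observed risk is 10% to 30% too low in relative terms, so that 40% reads as 34% at 15% missed. Equal loss also shrinks a true difference by the same fraction. This matters mainly because the pilot is to inform the power of the full trial.

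Bias between arms is possible but not shown, and no direction can be claimed. The conclusion assumes that some participants receive outside care unknown to the team, as the article's own limitation makes plausible, and that no contact or release beyond those described is planned.

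**What to change.** Revise the Aim 3 paragraph under Potential Limitations and Alternative Strategies in three ways:

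1. At the consent visit, before randomization, ask all participants in both arms for a release covering outside medical records through day 365 and for the names of their other providers. Asking before allocation keeps the decision independent of arm and does not rely on reaching the participant later.
2. At the end of follow-up, ask both arms the same short question about wounds and admissions at any facility, then request the records it points to.
3. For the event outcomes, class a participant with neither a confirmed contact nor records covering the year as unknown (missing), not as wound-free. Do not end follow-up at the last chart entry: wound-free people may generate fewer entries, so that rule would cut their time more and could inflate event rates.

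The cost is one release form, some records handling, up to 52 short calls by the existing coordinator, and probably a few refusals of the release. The change can go into the aim-3 ethics submission, which has yet to be made.
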